## Abstract

Background

Bifurcation coronary stenting (BCS) has unique therapeutic challenges. Several BCS strategies are prescribed for treatment, with conflicting data, and which is the best strategy for optimal short- and long-term outcomes remains a matter of debate. There is no systematic data from an Indian perspective in regard to patterns of BCS and its outcomes.

Methods and analysis

The Indian Bifurcation Stenting (IBIS) registry is a prospective, nationwide, endpoint-driven, investigator-initiated, multi-center, observational registry to compare the different bifurcation stent strategies, the effect of adjuvant techniques, and bifurcation anatomical differences in predicting short- and long-term clinical outcomes of bifurcation coronary interventions in India. A total of 1,000 patients from 20 clinical sites across the country will be enrolled in this study from September 2020 to August 2023. The primary endpoint will be the composite endpoint of major adverse cardiac events including cardiac death, target lesion myocardial infarction (MI), and ischemia-driven target lesion revascularization at the end of two years. The secondary endpoints include all causes of death, MI, target vessel revascularization, in-stent restenosis, stroke, and predefined procedural parameters. The safety endpoint is the occurrence of definite or probable stent thrombosis.

Conclusion

The aim of this prospective observational registry is to assess the practice patterns and clinical outcomes of patients undergoing coronary bifurcation lesion angioplasty in India. This will be extremely useful to provide an evidence-based insight as well as guidance to bifurcation angioplasty in India.

## Introduction

Approximately 15-20 % of all percutaneous coronary interventions (PCIs) involve bifurcation coronary stenosis [1,2], and it is often associated with technical challenges, lower procedural success, and worse clinical outcomes. There is no consensus regarding the appropriate strategy when treating coronary bifurcation stenosis (CBS). Multiple data from studies have provided an insight into different forms of stent implantation in CBS. The use of a single stent in provisional strategy to two stents in different techniques has been a challenge as to the choice of the strategy in different anatomical situations. A single-stent strategy is currently considered a standard stenting strategy for left main coronary artery bifurcation lesions because a two-stent strategy is associated with higher rates of adverse events such as target lesion revascularization (TLR) and stent thrombosis (ST) [3,4]. Additional techniques such as a final kissing balloon (FKB) and proximal optimization technique (POT) have resulted in better outcomes in bifurcation coronary stenting (BCS) [3,5]. Provisional stenting (PS) is the commonest and an approach by default in most of the bifurcation lesions, particularly when the side branch (SB) is small (diameter < 2.0 mm) and the main branch lesion length is small (usually <5 mm in length) [6-10]. But the effectiveness of PS for SBs more than 2.5 mm in diameter and the main vessel lesion length of more than 5 mm is underreported [11,12]. Moreover, currently, there are no angiographic criteria to differentiate the simple from complex CBS.

CBS vary in anatomy, plaque burden, the angle between branches, size of branches, and plaque shift post-angioplasty. Therefore, no two bifurcations are the same and a single strategy cannot be recommended for all bifurcations. There are many classifications for CBS and the most accepted one is the MEDINA classification. CBS is considered as true bifurcation stenosis when the SB is involved. A single-stent or PS strategy is planned in non-true bifurcations or when the SB is not relevant. Two-stent strategies are complex and indicated when the SB, which subtends a significant territory has high-grade stenosis. A number of studies have shown no additional benefit with a two-stent strategy over a single-stent or provisional strategy [13-16]. In addition, two-stent strategy is associated with more fluoroscopy, contrast volume, and biomarker release. However, there are CBS that warrant two-stent strategies from the outset depending on the lesion anatomy, plaque distribution, and bifurcation angle.

A provisional single-stent technique consists of stent implantation to the main vessel only with balloon angioplasty to the SB if the result is sub-optimal. However, in the case of suboptimal SB outcome, it may be necessary to stent the SB, converting the one-stent strategy to a two-stent technique. Various techniques for an upfront two-stent strategy have been described aiming at improving clinical outcomes. However, the best bifurcation strategy is still a matter of debate [17,18]. A recent meta-analysis found double kissing crush to be associated with fewer major adverse cardiac events (MACEs), compared to other two-stent techniques: Crush, Culotte, and T-Stenting/T and protrusion (TAP) [19].

Rationale of the study

BCS poses a therapeutic challenge and is associated with a worse clinical outcome and higher rates of peri-procedural and long-term complications. In India, approximately 0.7 million stents are implanted annually, but there is total lack of well-structured registry-based real-life data on CBS management. The National Interventional Council data of 2018 [20] showed that 4.32% of all coronary interventions in the country were BCS (total interventions: 438,351). This registry is planned to analyze the practice patterns regarding the treatment of BCS and outcomes of different techniques utilized for CBS in India. This outcome-based multi-center prospective observational registry, which is the first of its kind in our country, should provide proper information on the current prevailing BCS techniques and their impact on long-term clinical outcomes.

Objective of the study

The objective of the study is to compare the different bifurcation stent strategies, the effect of adjuvant techniques, and bifurcation anatomical differences in predicting short- and long-term clinical outcomes of bifurcation coronary interventions in India.

Primary endpoints

The composite endpoint of major adverse cardiac events (MACEs) includes cardiac death, target lesion myocardial infarction (MI), and ischemia-driven TLR at two years.

Secondary endpoints

Secondary clinical endpoints include in-hospital events as well as events at 1, 12, 24, and 36 months, which include cardiac death, all-cause mortality, and MI, target lesion MI (TLMI), TLR, ST, target vessel revascularization, any revascularization, and angina.

Secondary procedural endpoints at in-hospital and at 1, 12, 24, and 36 months include the number of stents implanted in BCS, total stent length in BCS, drug-eluting balloon, bifurcation strategy, SB rewiring, FKB, POT, POT-SB-POT (PSP) technique, and imaging modalities utilized for the procedure.

## Materials and methods

Study design and methods

This is an investigator-initiated prospective, multi-center, observational registry. Approximately 1,000 patients from 20 clinical sites will be enrolled in this study across India from September 2020 to August 2023. The selection of centers is based on a feasibility questionnaire send to the high-volume PCI centers across the country. All patients must meet all of the inclusion and exclusion criteria to be registered for the study (Figure 1).

**Figure 1 FIG1:**
[figure not shown]
Overall study design and endpoints for the Indian Bifurcation Stenting Registry CVA, cerebrovascular accident; MI, myocardial infarction

The trial is prospectively registered with the Clinical Trials Registry - India (CTRI/2020/08/027411).

Inclusion criteria

The inclusion criteria include the following:

1. Age more than 18 years

2. Any bifurcation coronary stenosis undergoing BCS

3. Two or bifurcations in the same patients are eligible, as long as only one bifurcation per vessel

4. Patients with another single lesion in different vessels could be treated as
 indicated

Exclusion criteria

The exclusion criteria include the following:

1. Patients with an expected survival of less than one year

2. Recent cerebrovascular accident

3. Allergy to aspirin, clopidogrel, or ticagrelor

4. Active cancer

5. Inability to provide consent

6. Patients who are already enrolled in randomized controlled trials or another registry

Study methodology

All eligible patients with significant CBS in at least one native coronary artery after angiography will be prospectively enrolled in the study. The angiographic data of the CBS will be documented by Quantitative Coronary Analysis (QCA) and the intended bifurcation strategy will be noted.

Post-procedure, the bifurcation strategy (one stent or two stents) utilized will be documented with the stent data and need for adjuvant devices such as a scoring balloon, rotablation, or intra-vascular lithotripsy. In addition, the sequential steps for one-stent or various two-stent strategies for bifurcation stenting and optimization will be recorded and include rewiring, final kissing, and POT or PSP. The use of coronary imaging for optimization of bifurcation stenting will also be recorded. The type of strategy for CBS and usage of intracoronary imaging will be at the operator's discretion.

The participants will be made aware of the fact that they are free to discontinue the study at any point in time, ask any queries related to the study which pertains to them, and will be given enough time to consider the information provided. The signed and dated patient informed consent will be obtained before any specific procedure for the study is performed. The investigator will store the original, signed patient informed consent form. A copy of the signed patient informed consent form will be given to the patients.

Core lab analysis

The angiographic quantitative coronary analysis will be performed for all patients enrolled in the study

Data quality and management plan

Privacy of Personal Data

The study will collect and process only the data required for fulfilling the objectives of the study, and no other personal data will be collected. All data will be dealt with in compliance with the applicable data privacy protection laws and regulations of the country. The informed consent includes explicit consent to processing the personal data and allowing direct access to his/her original medical records (source data/documents) for study-related monitoring, audit, Independent Ethics Committee/Institutional Review Board review, and regulatory inspection.

Data Reporting

Data should be recorded from each site to an electronic case report form, which is accessed by each investigator with the unique ID & password provided to him. Etrewo®, which is a secure web-based application for building and managing online databases, will be used for data management. The database will be maintained by BioQuest Solutions Private Limited (Bengaluru, Karnataka, India). Access will be via a secure website from each participating site.

The principal investigator of each site should ensure the accuracy, completeness, and authenticity of the data collection. Electronic case report form entries are ensured with the maintenance of anonymity of the data. Central data management will be done by the national principal investigator at Lisie Hospital, Kochi, Kerala, India. The source documents will be checked by designated clinical research assistants to verify the correctness of data entered into the eCRF (electronic case report form).

## Results

Statistical analysis plan

The two-sample t-test or the Mann-Whitney U-test will be utilized to compare the continuous variables depending upon the distribution. The chi-square test or Fisher exact will be utilized to analyze the categorical variables depending on the cell numbers. Adjusted and unadjusted Cox regression based on the intention-to-treat principle will be utilized to estimate the hazard ratio, which is the main effect measure. The final follow-up date for the primary endpoints will be as follows: a median of three years of follow-up is achieved and the last enrolled patient has been followed for at least one year. All the defined endpoints will be reviewed until death or lost to follow-up, and both intention-to-treat and per-protocol analyses will be utilized to access the combined outcomes. Cox proportional hazard regression analysis will be utilized to read the effects of baseline differences between groups. A two-sided p-value of less than 0.05 indicates statistical significance.

## Discussion

Ethical considerations

This study will be conducted in compliance with the ethical principles that have their origin in the Declaration of Helsinki and its revisions, the International Conference on Harmonization guidelines for Good Clinical Practice, and all federal and local laws. The investigator will be responsible for ensuring that this study is conducted according to the investigational plan and for protecting the rights, safety, and welfare of study patients under the investigator's care. This is a prospective study of human research. No experimental drug, procedure, or intervention is involved in the protocol. However, if any ethical issues arise during the study, the Institutional Ethics Committee will be consulted and their recommendations followed.

Withdrawal of patients

Investigator Withdrawal of Patients

If the principal investigator of the site determines that the best medical interest of the patient is not to continue within the study, then he/she may withdraw a patient from the study following due procedure.

Patient Withdrawal From the Study

If a patient decides to withdraw from the study, it will not affect their treatment. The patient will be advised to discuss their concern in detail with the investigator and can decide to withdraw from the study if they are willing to do so. In the case where the patient is lost to follow-up, effort must be made to contact the patient and determine the possible reason for discontinuation/withdrawal and documented. Data from patients who have withdrawn from the study will be included in the final data analysis, up to the point of their withdrawal.

Adverse Event Reporting

All serious adverse events, whether suspected to be related to the device or not, must be reported within 24 hours of obtaining knowledge of the event.

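### The protocol lets a site investigator's medical-grounds withdrawal end data collection in a registry without an intervention; this conflicts with its own follow-up rule and could cause informative censoring

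*Protocol article*

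**What the plan says.** Four statements in the protocol article bear on this point.

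- **Investigator withdrawal** (Discussion, Investigator Withdrawal of Patients). The principal investigator of a site who judges that the "best medical interest of the patient is not to continue within the study, then he/she may withdraw a patient from the study" may do so. The sentence then requires a due procedure, which the article does not describe.
- **Data after withdrawal** (Discussion, Patient Withdrawal From the Study). "Data from patients who have withdrawn from the study will be included in the final data analysis, up to the point of their withdrawal". The sentence stands under the heading for patient-initiated withdrawal, but its wording is general, and no other rule covers patients withdrawn by the investigator.
- **No assigned treatment.** Ethical considerations states that "No experimental drug, procedure, or intervention is involved in the protocol". Study methodology adds that "The type of strategy for CBS and usage of intracoronary imaging will be at the operator's discretion".
- **Follow-up and analysis** (Results, Statistical analysis plan). "All the defined endpoints will be reviewed until death or lost to follow-up". The main effect measure comes from the next rule: "Adjusted and unadjusted Cox regression based on the intention-to-treat principle will be utilized to estimate the hazard ratio".

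The primary endpoint is MACE, which "includes cardiac death, target lesion myocardial infarction (MI), and ischemia-driven TLR at two years".

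**The concern.** In a study that assigns treatment, withdrawing a patient for medical reasons can serve to stop that treatment. Here the study assigns none. Leaving the registry changes only whether the patient's outcomes are recorded, so the medical ground has no evident purpose, while the cost to the data is real.

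The ground for withdrawal is the patient's medical state. The endpoint includes cardiac death and target lesion MI, so a decision on that ground may depend on prognosis. If data stop there, Cox regression treats the patient as censored and assumes that the later risk equals that of comparable patients still followed. Where the later risk is higher, event rates are understated. Where such withdrawals differ between stent strategies, the hazard ratio is biased as well. Strategy is chosen rather than randomised and is known at the site, and there are 20 sites, so unequal use of the clause is possible. Adjustment for baseline covariates does not repair censoring that is driven by what happens after the procedure.

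**Working it through.** **Step 1: the passages side by side.**

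| Question | Discussion (withdrawal) | Results (analysis plan) |
|---|---|---|
| What ends endpoint follow-up? | Withdrawal, on the natural reading of the data rule | Death or loss to follow-up only |
| Who can end it? | The patient or the site principal investigator | Nobody by decision |
| Which patients count? | Withdrawn patients, up to withdrawal | Intention-to-treat, which sits badly with stopping follow-up by decision |

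A patient's own withdrawal of consent must be respected, so that part of the gap cannot be avoided. The investigator's decision is the part where the two sections give different answers without need.

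**Step 2: inputs.** There is no plan figure to reproduce. The article says "Approximately 1,000 patients from 20 clinical sites will be enrolled in this study" and gives no event rate, effect size, power or withdrawal rate. The following are therefore assumptions:

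- two-year MACE p without any change in hazard: 10% (range 5-15%);
- share w marked for withdrawal, at a time uniform over 0-2 years, withdrawn if still event-free: 1%, 2%, 5%;
- hazard after withdrawal multiplied by m = 1, 3 or 10.

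**Step 3: formula.** Let L = -ln(1 - p) be the two-year cumulative hazard. At p = 10%, L = 0.1054. Averaged over the withdrawal time, the true two-year risk of a patient marked for withdrawal is

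r = 1 - [exp(-L) - exp(-mL)] / [(m - 1)L].

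- m = 3: r = 1 - (0.9 - 0.729)/0.2107 = 18.9%.
- m = 10: r = 1 - (0.9 - 0.3487)/0.9482 = 41.9%.

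The true cohort risk is (1 - w)p + wr. Everyone has the base hazard until withdrawal, so a Kaplan-Meier estimate that censors at withdrawal targets p. The understatement is w(r - p).

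**Step 4: results at p = 10%, in percentage points.**

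| | w = 1% | w = 2% | w = 5% |
|---|---|---|---|
| m = 1 | 0 | 0 | 0 |
| m = 3 | 0.09 | 0.18 | 0.44 |
| m = 10 | 0.32 | 0.64 | 1.59 |

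A simulation of 1,000,000 patients per scenario agrees: 0.09, 0.17 and 0.45 for m = 3, and 0.32, 0.64 and 1.59 for m = 10. Over p = 5-15% with m = 3 or 10, the range is about 0.05 to 2.0 points. For scale, the sampling standard error of a 10% risk in 1,000 patients is sqrt(0.1 × 0.9/1000) = 0.95 points.

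**Step 5: comparison of strategies.** Take 5% withdrawn in one group, none in the other, and the same base risk of 10%. The simulated true ratio of two-year cumulative hazards is 1.04 (m = 3) or 1.16 (m = 10). The closed form gives ln(1 - 0.1044)/ln(0.9) = 1.05 and ln(1 - 0.1159)/ln(0.9) = 1.17; the difference is simulation error. With censoring at withdrawal, both are estimated as about 1.00.

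**The case against.** The strongest reply is that the text only permits withdrawal. It does not mention deterioration, expected frequency or any link to strategy. A withdrawal for non-cardiac illness need not predict cardiac death, target lesion MI or TLR. The required procedure may be defined in the full protocol, which a journal article would not repeat. The cut-off sentence stands under patient-initiated withdrawal, and the analysis section can be read as keeping every patient under review. The investigator is also responsible for the patient's welfare and may want some discretion.

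Much of this stands. The bias is a risk and not a certainty, it is zero when withdrawal is unrelated to prognosis, and it is small when withdrawals are few. The absence of withdrawal criteria is no finding here. Applying the cut-off to investigator withdrawals is an inference, though it is the only data rule on offer. None of this removes the conflict between the two sections.

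Three stronger readings are tempting, and the documents do not support them:

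- **That the clause does remove deteriorating patients.** It allows withdrawal, and nothing shows how it would be used.
- **That operators can remove their own poor results.** The power lies with the site principal investigator, while strategy is the operator's choice. The article does not say that they are the same person.
- **That the comparison could be grossly distorted.** Suppose 30 withdrawals, half with later MACE, all fall in one 300-patient group with a true rate of 10%. The rate becomes (30 - 15)/(300 - 30) = 5.6%, a ratio of 0.56. Those inputs are an invented extreme, and the sum drops withdrawn patients from the denominator although the protocol keeps their data up to withdrawal.

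**Conclusion.** The point holds in conditional form. The protocol permits withdrawal on medical grounds from a study without an intervention, and its only data rule stops at withdrawal. Its analysis section ends endpoint review only at death or loss to follow-up. The sections must be reconciled, because the first reading permits prognosis-related censoring in the main hazard-ratio analysis.

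The size rests wholly on assumed rates. At 10% base risk the understatement runs from a tenth of a point to 1.6 points, that is, from well below one standard error of the cohort risk to somewhat above it. The effect on the strategy comparison is modest even with one-sided withdrawal of 5%. It matters mainly if withdrawals are frequent, high-risk or unequal between strategies. This is a cheap improvement, not a flaw that undermines the registry.

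**What to change.** Add one statement to both the withdrawal and the analysis sections, for example: *An investigator's decision or a change in clinical care does not end endpoint follow-up. Follow-up ends only on death, loss to follow-up or the patient's own withdrawal of consent.*

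Where consent allows, continue to collect at least vital status and the MACE components from hospital records after any withdrawal. Privacy of Personal Data already describes consent to direct access to original records for monitoring, audit, ethics review and inspection. One added sentence would extend this to outcome data. Report the number, timing and reasons of withdrawals by strategy and site, so that readers can judge whether censoring could have affected the comparison.

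The cost is that consent sentence and slight extra data collection. The patient's right to leave is unchanged, and so is clinical care. The change is best made while patients can still be followed, since outcomes not collected after withdrawal may not be recoverable at analysis.

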## Conclusions

IBIS is the first nationwide registry intending to document the patterns of treatment of CBS and the outcome of BCS across India. This is the first planned registry that will provide organized data about CBS outcomes in our country where approximately 0.7 million stents are implanted annually but no systematic data exist about the patterns of treatment and outcomes.
